**Cycle 4 and subsequent even cycles (Vital signs and physical examination will be measured before administration on C4D1)**

- Day 21 on every cycle:

Vital signs, ECOG PS, physical examination;

Imaging examination (CT or MRI), CEA, NSE;

12-lead electrocardiogram;

Blood biochemistry, hemanalysis, urinalysis and stool tests (including occult blood), thyroid function, coagulation function, blood lipase, and amylase;

Biomarkers of myocardial injury;

Echocardiography;

Adrenal cortex function;

Questionnaire for HRQOL;

Concomitant medications, AEs, medication allocation, and recall.

**End-of-treatment (EOT)**

- ✓ Medical history: if any PCI or palliative chest radiotherapy during the trial period (if so, record start and end time, treatment duration, etc.);
- ✓ Vital signs, ECOG PS, and physical examination;
- ✓ Imaging examination (CT or MRI), CEA, and NSE;
- ✓ 12-lead electrocardiogram;
- ✓ Blood biochemistry, hemanalysis, urinalysis and stool tests (including occult blood), thyroid function, coagulation function, blood lipase, and amylase;
- ✓ Biomarkers of myocardial injury;
- ✓ Echocardiography;
- ✓ Adrenal cortex function;
- ✓ Questionnaire for HRQOL;
- ✓ Blood samples for the liquid biopsy-based biomarkers analysis;
- ✓ Concomitant medications, AEs, and medication recall.

**Post-treatment Follow-ups**

All subjects will be followed up every 8 weeks (including telephone follow-up) to collect data on other antitumor therapy and disease status. The treatment regimens, cycles, and outcomes of any other treatment must be recorded during the trial. Post-treatment follow-up will be conducted until

death. Reasons and the date of death will be recorded for overall survival analysis.

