## 1.6 Human Tolerance, Pharmacokinetics, and Other Clinical Studies

Patients with advanced malignancies without standard therapy were included in phase I clinical study of TQB2450. Exploratory studies with 6 dose groups including 1 mg/kg, 3 mg/kg, 10 mg/kg, 20 mg/kg, 30 mg/kg, and a fixed dose of 1200 mg were successively carried out according to the dose increment design. Patients were administered TQB2450 once every 3 weeks until progressive disease (PD) or intolerable toxicity.

Thirty-three patients with various advanced tumors were enrolled by February 2019. Preliminary results showed that the majority of the receptor occupation was more than 90% at day 21 of medication in the 3-30 mg/kg dose group. It suggested that TQB2450 could maintain saturation until the next dose. After intravenous injection of TQB2450, drug exposure and  $C_{max}$  showed good linearity in the 3-20 mg/kg dose group, and an estimated half-life was 320 hours at 1200 mg dose.

The patients in all dose groups had good tolerance. The adverse events (AEs) mainly were abnormalities in various examinations, most of which were grade 1 or 2. No dose-limiting toxicity (DLT) was observed within 21 days after medication.

The short-term efficacy including objective remission and long-term tumor control was observed in patients with advanced Hodgkin's lymphoma and various solid tumors (including lung cancer, kidney cancer, etc.), which demonstrated the promising antitumor activity of TQB2450. The recommended regimen was TQB2450 of 1200 mg every 3 weeks according to the results of the Phase I study.

Clinical studies are performed based on the above results, including TQB2450 monotherapy in relapsed refractory Hodgkin's lymphoma and mediastinal large B-cell lymphoma, and TQB2450 plus chemotherapy as the first-line therapy in head and neck squamous cell carcinoma. In parallel, numerous exploratory studies of TQB2450 plus anlotinib in soft tissue sarcoma and hepatobiliary tract tumors have been initiated.

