### 3. Inclusion Criteria and Endpoints

#### 3.1 Inclusion and Exclusion Criteria

##### **Inclusion criteria:**

A subject can participate in the study only if all the following criteria are met:

- (1) Pathologically confirmed diagnosis of ES-SCLC per Veterans Administration Lung Study Group (VALG) stage;
- (2) No previous systemic treatment for ES-SCLC;
- (3) Patients with prior chemoradiotherapy for limited-stage SCLC must have received radical therapy and have at least 6 months of no treatment interval between the end of chemotherapy, radiotherapy, or chemoradiotherapy and the diagnosis of ES-SCLC (calculated as the end time of the last chemotherapy cycle or the last radiotherapy);
- (4) At least one measurable lesion based on RECIST v1.1; a previously irradiated lesion can be considered as a measurable lesion only if it has made definite progress after radiotherapy and is not the only one;
- (5) Age 18-75 years; ECOG PS of 0-1; predicted life expectancy of  $\geq 3$  months;
- (6) Adequate function of the important organs as evidenced by the following:
  - a) Hemanalysis (no blood transfusion within 14 days, no correction with hematopoietic stimulator drugs): hemoglobin (Hb)  $\geq 90$  g/L; absolute neutrophil count (ANC)  $\geq 1.5 \times 10^9$ /L; platelets (PLT)  $\geq 75 \times 10^9$ /L; white blood cell count (WBC)  $\geq 3 \times 10^9$ /L;
  - b) Biochemistry: alanine aminotransferase (ALT) and aspartate aminotransferase (AST)  $\leq 2.5 \times$  upper limit of normal value (ULN) or  $\leq 5 \times$  ULN for patients with liver metastases; total bilirubin (TBIL)  $\leq 1.5 \times$  ULN or  $\leq 3 \times$  ULN for patients with Gilbert syndrome; Creatinine (Cr)  $\leq 1.5 \times$  ULN or creatinine clearance rate (CCr)  $\geq 50$  mL/min;
  - c) Coagulation function: activated partial thromboplastin time (APTT), international normalization ratio (INR), or prothrombin time (PT)  $\leq 1.5 \times$  ULN;
  - d) Doppler ultrasound assessment: left ventricular ejection fraction (LVEF)  $\geq 50\%$ ;
- (7) Women of childbearing potential and men must agree to contraception for the duration of study treatment and 6 months after the last dose of study treatment, such as an intrauterine device (IUD), birth control pills, or condoms for women; women must have a negative serum pregnancy test within 7 days prior to the study grouping and be on-lactating;

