#### **3.2.2 Handling of Participant Withdrawals**

Investigators should clearly collect the reason and time of withdrawal, conduct corresponding observation and evaluation of the withdrawn subjects, complete the evaluation content when withdrawing from the study as specified in the study plan, fill in the corresponding original records, and describe the reasons for withdrawal. Subjects who discontinue the study should continue to be

followed for AEs. If possible, these subjects should continue to follow up AEs until it recovers to the baseline level or the investigator believes that follow-up observation is unnecessary.

During the study period, all subjects who received the drug but did not complete the relevant study content of the protocol should have their last examination results transferred to the final result. Subjects who did not follow up as required and evidence of contact should be recorded in the corresponding original records and electronic data collections (EDCs; such as time and date of telephone contact, mailing receipt of registered mail, etc.) and properly preserved.

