## 6. Biological Samples

### 6.1 Serum Anti-TQB2450 Antibody (ADA) Assessment

The scheduled intervals for immunogenicity monitoring will be based on the administration time of TQB2450. If the administration time of TQB2450 is delayed, blood sampling for immunogenicity will be delayed accordingly.

For subjects with positive ADA, the neutralization antibody will be detected.

Blood samples (5 mL) will be collected pre-dose (within -15 min) at cycles 1, 2, 5, 7, and day 90 ( $\pm 7$ ) after the last administration. Samples will be collected in separation gel procoagulant tubes for 30 min and then centrifuged at 3000 g for 10 min. The obtained serum will be stored for measuring the immunogenicity and blood concentration of TQB2450. Detailed procedure is listed in the SOP provided by the central laboratory.

Additional blood samples (5 mL) will be considered for subjects with unexpected irAEs to measure the immunogenicity and blood concentration of TQB2450. However, if the time of sampling is less than 24 hours from the latest collection, the additional sampling could be exempted.

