## 8. Concomitant Medications

Any protocol-allowed medications taken by subjects for concomitant disease (except for study drugs) during the trial are concomitant medications and will be recorded on the medical record and eCRF. The following list of the recordkeeping time and requirements for concomitant medications is provided as guidance.

| Recordkeeping time                                                                                                    | Recordkeeping requirements                                                                                                                                                                                                  |
|-----------------------------------------------------------------------------------------------------------------------|-----------------------------------------------------------------------------------------------------------------------------------------------------------------------------------------------------------------------------|
| From the ICF signature to the first dose of the study drug                                                            | All medications or meaningful nondrug treatments: generic name, doses, the reason for treatment with this medication, start and stop date of this medication, or whether this medication was continued at study enrollment. |
| From the first dose of the study drug to the study withdrawal                                                         | All medications or meaningful nondrug treatments.                                                                                                                                                                           |
| From the study withdrawal to 28 days after the last dose or starting other antitumor therapy (whichever occurs first) | All medications related to AE disposition.                                                                                                                                                                                  |
| Post-treatment phase (from 28 days after the last dose or starting other antitumor therapy to the end of the trial)   | All medications related to anti-tumor therapy (in the OS follow-up section after study withdrawal).                                                                                                                         |

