### **Pregnancy**

If a female subject or a female partner(s) of a male subject becomes pregnant during the trial, the investigator(s) should be informed immediately. Investigator(s) are required to report to the sponsor within 24 hours of learning of its occurrence. Pregnant subjects should immediately stop using the study drug. The investigator should counsel the patient, and discuss the risks of continuing the pregnancy and the possible effects on the fetus. Pregnant subjects will be monitored until the end of pregnancy. All pregnancies within 30 days of the last administration will be reported to the

investigator(s).

Both induced and spontaneous abortions should be reported as SAEs. Any congenital anomalies/birth defects in infants born to female subjects or female partners of male subjects who had taken study drugs should be reported as SAEs.

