### **10.4 Follow-up of AEs**

Investigator(s) are required to follow up all AEs until any of the following occurs:

- AEs resolve to baseline;
- No further remission will be expected by the investigator(s);
- Death;
- Lost to follow-up;
- AEs that are not related to the study treatment confirmed by the investigator(s);
- Starting new antitumor treatment;
- End of clinical or safety data collection, or the database lock;
- No clinical or safety data are collected, or the database is eventually closed.

The outcomes of each AE (including the date of resolution and death) need to be recorded in the CRF/eCRF.

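### The AE, SAE and pregnancy reporting periods are undefined or inconsistent and, as written, too short for TQB2450

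*Protocol*

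**What the plan says.** Section 7 lists AEs among the items at every treatment visit and at end of treatment. For the period after that it says "All subjects will be followed up every 8 weeks (including telephone follow-up) to collect data on other antitumor therapy and disease status", and adds the date and reason of death. AEs are not on that list.

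Sections 10.1 and 10.3 tie AE recording to a reporting period, and section 10.6 refers to a safety reporting period. Neither is given a length. The one dated limit is in the section 8 table, where medication for AEs is recorded "From the study withdrawal to 28 days after the last dose or starting other antitumor therapy (whichever occurs first". After that point only antitumor medication is recorded.

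Section 10.4 lists several conditions, any one of which ends follow-up of an AE. One of them is "Starting new antitumor treatment". Section 3.2.2, on subjects who discontinue, says that "these subjects should continue to follow up AEs until it recovers to the baseline level", qualified by feasibility and by the investigator's judgment that observation is no longer needed.

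On pregnancy, section 10.3 says "All pregnancies within 30 days of the last administration will be reported" to the investigator. Inclusion criterion 7 requires contraception until "6 months after the last dose of study treatment".

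Two other statements bear on how long exposure lasts. Section 1.6 reports that "an estimated half-life was 320 hours at 1200 mg dose". Section 6.1 says "Blood samples (5 mL) will be collected pre-dose (within -15 min) at cycles 1, 2, 5, 7, and day 90" after the last administration; these samples serve both immunogenicity and TQB2450 concentration.

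**The concern.** Safety and tolerability are secondary endpoints, and the contrast between arms depends on every site watching for the same length of time. With no stated length, one site may stop asking about AEs at the end-of-treatment visit, another at 28 days, and a third when second-line therapy begins. An SAP can define which recorded events count as treatment-emergent, but it cannot recover events that sites were never told to collect.

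A window of about 28 days would also be short for a long-lived antibody. Immune-related events that begin, worsen or resolve after the last dose could go unrecorded, or be recorded without their final grade and outcome. For pregnancy, a site that follows the 30-day sentence literally would not report a conception in months 2 to 6, although contraception is still required then.

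**Working it through.** The protocol states no figure that can be reproduced here. The check sets its time limits side by side and applies its own half-lives.

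**1. Time limits after the last dose**

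| Item | Section | Limit |
|---|---|---|
| Last scheduled AE item | 7, EOT | End-of-treatment visit |
| AE reporting period | 10.1, 10.3 | Named, no length |
| Safety reporting period | 10.6 | Named, no length |
| Medication for AEs | 8 | 28 days or new therapy, whichever is earlier |
| Pregnancy reporting | 10.3 | 30 days |
| Live-vaccine restriction | 8.1 | 60 days |
| ADA and concentration sample | 6.1 | Day 90 (±7) |
| Contraception | 3.1 (7) | 6 months |

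The day-90 sample has no matching visit in section 7, so the sampling and visit schedules do not agree.

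**2. Drug remaining at these times**

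Inputs: TQB2450 half-life 320 h (section 1.6); anlotinib half-life 116 h, the single-dose mean at 12 mg (Table 1.9.2-1). Assumption: first-order decay, so the fraction remaining at day d is 0.5^(24d / half-life).

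TQB2450:
- Day 28: 24 × 28 / 320 = 2.10 half-lives, 23.3% remaining.
- Day 30: 24 × 30 / 320 = 2.25 half-lives, 21.0% remaining.
- Day 60: 24 × 60 / 320 = 4.50 half-lives, 4.4% remaining.
- Day 90: 24 × 90 / 320 = 6.75 half-lives, 0.9% remaining.
- Five half-lives: 5 × 320 / 24 = 66.7 days.

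Anlotinib:
- Day 28: 24 × 28 / 116 = 5.79 half-lives, 1.8% remaining.
- Five half-lives: 5 × 116 / 24 = 24.2 days.

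A 28-day window therefore covers washout of anlotinib but not of TQB2450. The estimate of 320 h comes without an interval. For five half-lives to fit into 28 days, the half-life would have to be at most 24 × 28 / 5 = 134 h, less than half the stated value.

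**3. The new-treatment stop**

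Section 10.4 governs follow-up of events already recorded. An open event that is dropped when new therapy starts keeps its place in the incidence count, with its grade to date. What is lost is any later worsening and the outcome. For a discontinued subject with an open event who starts second-line therapy, section 10.4 permits stopping, while section 3.2.2 asks for continued follow-up where possible. The site cannot tell which rule governs.

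**4. Pregnancy**

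Taking a month as 30 days, 30 / 180 = one sixth of the contraception period is covered by the 30-day sentence. Section 10.3 also requires a report within 24 hours of any pregnancy during the trial, and section 10.6 has pregnancy in patients or spouses reported as an SAE with no end date. The wording is thus inconsistent, and only the 30-day sentence is restrictive.

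**The case against.** The strongest reply is that no rule in the protocol ends AE collection at end of treatment. Section 10.7 requires any SAE to be reported within 24 hours of awareness with no end date, section 3.2.2 continues AE follow-up after discontinuation, and the section 8 table implies about 28 days. The irAE appendix cited in section 10.8 is not available here and might say more. This stands as far as it goes: the defect is an undefined window with conflicting cues, not a stated stop at end of treatment.

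A reader might also infer that the loss is one-sided, mainly in the TQB2450 arm. Only intervention arm 1 receives the antibody. In Table S3, irAEs leading to any discontinuation occurred in 20, 3 and 4 patients (TQB2450 arm, anlotinib arm, control), so a greater effect in that arm is plausible. But the rules are the same in all three blinded arms, and Table S3 reports irAEs of any grade in 42.7%, 27.5% and 19.1%, so investigator-labelled events are not confined to one arm. The planned PFS hazard ratios of 0.60 and 0.65 imply earlier progression in the control arm, so a new-therapy cut-off could shorten observation more there. No late-onset rate is given.

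Nor does the planned control median PFS of 4 months show that most patients start new therapy within 90 days of their last TQB2450 dose. The control arm receives no TQB2450, PFS does not start at the last dose, and the document gives no interval from last dose to new therapy.

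Finally, residual drug, vaccine limits and antibody sampling do not themselves define an AE window. That is fair. They show that 28 to 30 days is out of line with the protocol's other time limits; they do not fix a unique correct length.

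**Conclusion.** The point holds as a defect of definition and consistency. No AE collection is scheduled after end of treatment, the two reporting periods have no length, and the only dated cues, 28 and 30 days, fall well short of the roughly 67 days that five TQB2450 half-lives take. At those cues 23% and 21% of the drug remains. The new-treatment stop conflicts in part with section 3.2.2 and can truncate the outcome and later worsening of open events, but not reduce their incidence. The 30-day pregnancy sentence covers about one sixth of the contraception period and conflicts with open-ended wording elsewhere.

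Late immune events may be missed or incompletely followed. A larger effect in the TQB2450 arm is plausible, but neither its size nor the net direction between arms can be computed. The residual-drug figures rest on the stated half-life and first-order decay; five half-lives is a convention, not a protocol statement. This should be corrected. It does not affect the primary efficacy analyses.

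**What to change.** These changes concern data collection only.

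- **Reporting period.** Define one period for SAEs and immune-related AEs, identical in all arms, to day 90 after the last TQB2450/placebo dose, whether or not new antitumor therapy has started. Use the same definition in sections 8, 10.1, 10.3 and 10.6.
- **Collection points.** Add the day-90 blood draw from section 6.1 to the section 7 schedule, with an AE enquiry. Add AE questions to the existing 8-week contacts. If counted from the last dose, these fall near days 56 and 112, so the later contact can ask back to day 90 when the draw was missed.
- **Open events.** Remove the start of new antitumor treatment as a stop for open SAEs and immune-related AEs in section 10.4, and reconcile that list with section 3.2.2.
- **Pregnancy.** Align the reporting period in section 10.3 with the 6-month contraception period in inclusion criterion 7 and with the wording of section 10.6.
- **Tabulation.** Record the start date of new therapy and report events before and after it separately.

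The cost is amendment wording, AE questions at contacts that mostly exist already, and one visit entry for a sample already planned. The real downside is that events after second-line therapy are harder to attribute; the separate tabulation makes this visible but does not remove it.

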## 8. Concomitant Medications

Any protocol-allowed medications taken by subjects for concomitant disease (except for study drugs) during the trial are concomitant medications and will be recorded on the medical record and eCRF. The following list of the recordkeeping time and requirements for concomitant medications is provided as guidance.

| Recordkeeping time                                                                                                    | Recordkeeping requirements                                                                                                                                                                                                  |
|-----------------------------------------------------------------------------------------------------------------------|-----------------------------------------------------------------------------------------------------------------------------------------------------------------------------------------------------------------------------|
| From the ICF signature to the first dose of the study drug                                                            | All medications or meaningful nondrug treatments: generic name, doses, the reason for treatment with this medication, start and stop date of this medication, or whether this medication was continued at study enrollment. |
| From the first dose of the study drug to the study withdrawal                                                         | All medications or meaningful nondrug treatments.                                                                                                                                                                           |
| From the study withdrawal to 28 days after the last dose or starting other antitumor therapy (whichever occurs first) | All medications related to AE disposition.                                                                                                                                                                                  |
| Post-treatment phase (from 28 days after the last dose or starting other antitumor therapy to the end of the trial)   | All medications related to anti-tumor therapy (in the OS follow-up section after study withdrawal).                                                                                                                         |

